## Methods

### Study design

The PSP PTSI Study uses a longitudinal prospective sequential experimental cohort design [59–61] that engages each participant for approximately 16 months. Several practical constraints prohibited a randomized controlled trial, including resource limitations and probable interactions between PSP during and after training. Nevertheless, evidence from meta-analyses suggests against statistically significant differences between observational studies and randomized controlled trials, irrespective of specific design [62, 63], and the RCMP Study design is expected to generate results relative to a control group [56].

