**Methods:**

The current protocol paper describes the PSP PTSI Study (i.e., design, measures, materials, hypotheses, planned analyses, expected implications, and limitations), which was originally designed to evaluate an evidence-informed, proactive system of mental health assessment and training among Royal Canadian Mounted Police for delivery among diverse PSP (i.e., firefighters, municipal police, paramedics, public safety communicators). Specifically, the PSP PTSI Study will: (1) adapt, implement, and assess the impact of a system for ongoing (i.e., annual, monthly, daily) evidence-based assessments; (2) evaluate associations between demographic variables and PTSI; (3) longitudinally assess individual differences associated with PTSI; and, (4) assess the impact of providing diverse PSP with a tailored version of the Emotional Resilience Skills Training originally developed for the Royal Canadian Mounted Police in mitigating PTSIs based on the Unified Protocol for the Transdiagnostic Treatment of Emotional Disorders. Participants are assessed pre- and post-training, and then at a follow-up 1-year after training. The assessments include clinical interviews, self-report surveys including brief daily and monthly assessments, and daily biometric data. The current protocol paper also describes participant recruitment and developments to date.

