### Strengths and limitations

The PSP PTSI Study has several strengths including: (1) longitudinal design elements that can inform causal relationships; (2) prospective design elements that can inform predictive and proactive discussions associated with PPTE; (3) relatively large sample sizes; (4) ongoing multimodal assessments of environmental factors and individual differences, including PPTE exposures, occupational stressors, and social stressors; (5) inter-rater reliability assessments for clinical interviews; and, (6) being an ecologically valid test of the entire RCMP Protocol, including the ERST [56] across diverse PSP.

The PSP PTSI Study also has several necessary limitations. A truly randomized design was impossible because of how PSP interact within their professional environments. The already complex PSP environments were made more so by contemporary challenges with staffing and implementation requirements to protect public safety during the COVID-19 pandemic. Results from the RCMP Study will help address such limitations [56], as will having founded the ERST on the UP content that was based on randomized controlled studies [62, 63]. There is no obfuscation of the intended outcomes from ERST, which will create unknowable influence from expectancy effects. Direct research on such impacts remains nascent [117], but results suggest little or no difference between open and closed label designs when participants are provided with a sufficient study design rationale (e.g., [118]). The assessments are uncommonly detailed, which may produce intermittent participant response fatigue; however, participants were expressly informed about the rationale for the assessment details, which may help sustain morale. The detailed assessments also increase Type I error risks from spurious correlations [119]. The pre-registration of hypotheses, as well as the a priori provision of expected results in the current protocol paper are expected to mitigate Type I error risks and protect against equally problematic Type II error risks [119]. The voluntary nature of participation creates an unknowable influence from self-selection biases. The sample size, analytic plan, relatively short follow-up period, and provision of feedback through an electronic mental health record are designed to offset attrition.

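### The observational-versus-randomized argument in Study design does not supply the missing comparator, so T1–T2 change cannot be credited to ERST as hypothesis 2 does

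*Protocol article*

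**What the plan says.** Study design (protocol article) describes the study thus: "The PSP PTSI Study uses a longitudinal prospective sequential experimental cohort design". The abstract gives the measurement plan: "Participants are assessed pre- and post-training, and then at a follow-up 1-year after training". The reason for not randomizing is practical: "Several practical constraints prohibited a randomized controlled trial, including resource limitations and probable interactions between PSP during and after training". Two offsetting arguments follow in one sentence. The first is that "evidence from meta-analyses suggests against statistically significant differences between observational studies and randomized controlled trials, irrespective of specific design", citing references 62 and 63. The second is that "the RCMP Study design is expected to generate results relative to a control group".

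Strengths and limitations returns to the subject. It concedes that randomization was not possible and that self-selection has an unknown influence. On expectancy it says: "There is no obfuscation of the intended outcomes from ERST, which will create unknowable influence from expectancy effects", and answers that "results suggest little or no difference between open and closed label designs when participants are provided with a sufficient study design rationale". It also says that RCMP Study results will help, as will "having founded the ERST on the UP content that was based on randomized controlled studies [62, 63", which carries the same two references. The same section lists the longitudinal design's ability to inform causal relationships as a strength.

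Hypothesis 2 (Hypotheses) expects lower risk, more resilience and better mental health from T1 to T2, and makes ERST the cause of that change.

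**The concern.** The first argument treats a lack of statistical significance as evidence that two kinds of study agree. Even if they did agree on average, that would concern effect estimates. A cohort compared only with its own baseline produces a change. To turn that change into an effect, one must know what would have happened without ERST, and nothing in the planned analysis provides this.

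What is at stake is the conclusion. If the argument is accepted, a significant T1–T2 change will be read as the effect of ERST, although anything else that moved scores over the same months is part of it. Readers deciding whether to scale up the training would then rely on an attribution that the design cannot support.

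**Working it through.** **1. Is there a contrast of ERST with no ERST?** Data collection time frame places T1 before training, T2 about 16 weeks after training starts, and T3 one year after T2. No untrained, waitlisted or delayed group is described. The design label contains the word sequential, but no staggered comparison is set out. The power section for continuous outcomes covers time, sector and sector by time. Planned analyses tests differences between sectors and change over time. Sectors are not arms, so the only ERST contrast is before versus after.

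**2. Can the RCMP Study stand in?** By Background, that study adds ERST to the RCMP Cadet Training Program and compares it with standard training. Here the participants are serving personnel with at least 3 years in their sector, and the ERST has been adapted. Planned analyses contains no step that uses the RCMP control group.

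**3. Does the article itself name other causes of T1–T2 change?** It names three.
- Assessment with feedback: hypothesis 3 expects completing assessments to predict improvement, and Expected implications lists self-monitoring and earlier access to care as benefits.
- COVID-19: Current study status reports increased workload. Collection began on October 20, 2021, and T2 was expected to end by August 19, 2022.
- Expectancy, which Strengths and limitations calls unknowable.

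These can push in either direction. Favourable drift would imitate an ERST effect and unfavourable drift would hide one.

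**4. The plan's own figure.** Inputs from the continuous-outcomes power section: N = 200 in 4 sectors of 50, correlation ρ = 0.5, α = 0.05, power 80%, stated detectable effect for time 0.10. For a repeated-measures F test of time with m occasions, λ = f²·N·m/(1 − ρ). With m = 2 and f = 0.10, λ = 0.01 × 200 × 2/0.5 = 8. Solving for 80% power gives f = 0.0995 with m = 2 and 0.090 with m = 3. The stated 0.10 reproduces with two occasions. It is a detectable change over time, not a detectable difference between ERST and no ERST. With two occasions f = d/2, so f = 0.10 is a change of d = 0.20 SD.

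**5. Illustration with no ERST effect.** Assume that causes other than ERST shift the mean by d SD. The paired test has noncentrality d·√N/√(2(1 − ρ)). At ρ = 0.5 the denominator is 1, leaving d·√N. N = 160 is the 40 per sector at Time 2 given in the sample size section (4 × 40).

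| Assumed shift (SD) | d·√200 | P(significant), N = 200 | d·√160 | P(significant), N = 160 |
|---|---|---|---|---|
| 0 | 0 | 0.05 | 0 | 0.05 |
| 0.10 | 1.41 | 0.29 | 1.26 | 0.24 |
| 0.15 | 2.12 | 0.56 | 1.90 | 0.47 |
| 0.20 | 2.83 | 0.80 | 2.53 | 0.71 |
| 0.30 | 4.24 | 0.99 | 3.79 | 0.97 |

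A concurrent control group with the same drift would hold the probability at 0.05 in every row. In the three-occasion F test at N = 200, a shift of 0.20 SD at both T2 and T3 corresponds to f = 0.094 and is detected with probability 0.84. Drift as large as the change the study is sized to detect therefore cannot be told apart from that change.

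**The case against.** The article is open about much of this: it concedes non-randomization, expectancy and self-selection. It also offers more than a bare two-point contrast. Up to 15 monthly assessments allow trend analyses, and one hypothesis relates change to engagement with ERST content. Those features stand as useful supplements, but neither is a comparison with people who did not receive ERST.

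The illustration is also open to challenge. It is the ordinary power of a paired test, the drift sizes are assumed, and the planned mixed models add covariates, sector clustering and familywise error control. This is fair. The figures show sensitivity to drift; they do not estimate how much drift occurred.

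Four stronger readings are tempting, and the documents do not support them.
- *That the open-versus-closed-label sentence excuses the missing control group.* It is offered only against expectancy. It says nothing about the other causes, but it is not put forward as a substitute for a comparator.
- *That the cited meta-analyses cannot apply to this design.* Which designs they covered cannot be seen from the article. What can be said is that the argument as written does not establish the conclusion.
- *That one use of references 62 and 63 must be wrong.* In Strengths and limitations the citation closes a sentence about coping without randomization, so it may repeat the earlier argument instead of describing trials of the parent treatment. The placement is ambiguous and needs reconciling.
- *That regression to the mean inflates the change.* The eligibility criteria set no symptom threshold, and the exclusions remove some severe cases. Volunteers might still have joined when unwell, but nothing in the article shows it.

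**Conclusion.** The concern holds in a limited form. The equivalence sentence does not justify reading T1–T2 change as an effect of ERST, and the external RCMP control group does not repair this because no planned analysis uses it. Hypothesis 2 and the causal-strength statement therefore claim more than the design can deliver, and the list of limitations omits the one that matters most here.

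If ERST did nothing and other causes moved scores by 0.10 to 0.20 SD, a significant change would appear 29% to 80% of the time at n = 200 and 24% to 71% at n = 160. This rests on assumed drifts, the article's correlation of 0.5 and two-sided alpha of 0.05, and a simple paired test in place of the planned mixed model. The logical point does not depend on those figures.

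This is not a demand for a randomized trial. The study remains informative about change following ERST, differences between sectors and participants' reactions to the training.

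**What to change.** - Study design: delete the sentence part that appeals to non-significant differences between observational and randomized studies. If the RCMP Study control group is kept as support, say that it is external and is not part of the planned analyses.
- Hypotheses: reword hypothesis 2 so that it predicts change following ERST, without making ERST the cause.
- Strengths and limitations: qualify the statement that the design can inform causal relationships. Add, for example: T1–T2 change has no concurrent comparator; it may include effects of assessment and feedback, changing workload during COVID-19 and expectancy; it will not be interpreted as an ERST effect comparable with randomized estimates.
- In the same section, state that the open-versus-closed-label sentence concerns expectancy only.
- Reconcile the use of references 62 and 63 between Study design and Strengths and limitations.

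The cost is wording only; sample size, data collection and models are unchanged. The downside is a weaker claim about what the study can show.

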### ERST adaptation

A focus group was conducted with PSP PTSI Study stakeholders prior to the first training session to inform adaptation and tailoring of the ERST, shifting from RCMP-focused content to engage a broader PSP audience. The work included identification of gender- or sex-related considerations. The focus group met three times over 3 days and was led by one of the co-authors ([name]). The focus group participants included a firefighter, two paramedics, a police officer, and a public safety communicator. The stakeholder feedback was transcribed and analyzed to identify necessary adaptations, all of which were completed initially by another co-author ([name]), reviewed by the stakeholders, and the reviewed by another co-author ([name]) to check for fidelity with the UP. The updated content was reviewed by the PSP ERST trainers who made additional revisions, all of which were reviewed by the same co-author team ([name], [name], [name]) before finalizing the materials.

### Ethics approval

The University of Regina Ethics Board provided initial approval on May 28, 2021 (File #2020-226) and renewed on May 28, 2022. The trial is relatively short-term, relatively low risk, focused on symptom relief, and is being independently overseen by the University of Regina Research Ethics Board; as such, a dedicated data monitoring committee was created.

#### Sample size requirements and power analyses

Power analyses for a cluster randomized trial were performed using SAS version 9.3 (SAS Institute Inc., Cary, NC, US) and RMASS. Based on these analyses, a sample of 40 participants per sector at Time 2 will provide adequate power (i.e., > 80%) [65, 66]. Power analyses assumptions were: (1) clustering of participants into sectors; (2) repeated measures in participants over time (i.e., clustering within participants); and, (3) attrition (i.e., loss to follow-up).

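### The 40-per-sector sample rests on power for a cluster randomized trial, which this study is not; the power calculations that fit the design use 50 per sector

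*Protocol article*

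**What the plan says.** Sample size requirements and power analyses opens with "Power analyses for a cluster randomized trial were performed using SAS version 9.3" and RMASS, and concludes that "a sample of 40 participants per sector at Time 2 will provide adequate power (i.e., > 80" per cent). The listed assumptions are "1) clustering of participants into sectors", repeated measures within participants, and "3) attrition (i.e., loss to follow-up"). No arms, effect size, intraclass correlation, alpha or attrition rate are given there.

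The design is described differently elsewhere. Study design states "The PSP PTSI Study uses a longitudinal prospective sequential experimental cohort design" and "Several practical constraints prohibited a randomized controlled trial". It leaves a controlled comparison to a separate study: "the RCMP Study design is expected to generate results relative to a control group". Strengths and limitations repeats that "A truly randomized design was impossible because of how PSP interact within their professional environments". In Hypotheses, the second and fifth concern change over time in the participants. Planned analyses describes mixed models for time and sector and names no arm term.

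Two further subsections give power at 50 per sector, 200 in total. For continuous outcomes the detectable effects are 0.10 (time), 0.11 (sector by time) and 0.19 (sector). For categorical outcomes the odds ratios are 0.66 overall and 0.39 by sector.

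**The concern.** The only stated justification for 40 per sector is attributed to a design that the same article says could not be used. Because that paragraph names no contrast or effect, the design label is the reader's only guide to what the 80% covers, and the label is wrong for this study.

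Two things are at stake. First, the second hypothesis attributes T1 to T2 change to the training. A power statement labelled as coming from a cluster randomized trial, set beside that hypothesis, lends it a support that this design does not supply. Second, 40 per sector is the number put forward for Time 2, while the calculations that do fit the design assume 50. The article therefore gives no usable power statement at the number it calls adequate. It also aims to support replication, so others may carry the 40 forward.

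**Working it through.** **The stated 80%.** It cannot be reproduced: effect size, intraclass correlation, arms, alpha and attrition rate are all absent from that paragraph. (Going from 50 to 40 would be a 20% loss, since 50 × 0.8 = 40, but the article does not say so.)

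**The continuous-outcome figures at N = 200.**

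Inputs from that subsection: alpha 0.05, power 80%, within-person correlation r = 0.5, k = 4 sectors, N = 200. The number of time points m is 3 (T1, T2, T3). The article calls the effect a standardized difference in means. I read it as Cohen's f, the G*Power repeated-measures input, because that reading reproduces the figures.

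Noncentral F with
- time: λ = f²·N·m/(1 − r), df = m − 1 and (N − k)(m − 1)
- sector by time: same λ, df = (k − 1)(m − 1) and (N − k)(m − 1)
- sector: λ = f²·N·m/(1 + (m − 1)r), df = k − 1 and N − k

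Effects detectable at 80% power with N = 200:
- time: 0.090 with m = 3, or 0.0995 with m = 2 (stated 0.10)
- sector by time: 0.107 with m = 3 (stated 0.11)
- sector: 0.1925 with m = 3 (stated 0.19)

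The stated figures reproduce to rounding. The time figure matches two time points and the other two match three.

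**The same model at 40 per sector, N = 160, m = 3.**

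| Contrast | Stated f | λ | df | Power at 160 | Power at 200 | f detectable at 160 |
|---|---|---|---|---|---|---|
| Time | 0.10 | 0.01 × 160 × 3/0.5 = 9.60 | 2, 312 | 79% | 88% | 0.101 |
| Sector by time | 0.11 | 0.0121 × 160 × 3/0.5 = 11.62 | 6, 312 | 71% | 82% | 0.120 |
| Sector | 0.19 | 0.0361 × 160 × 3/2 = 8.66 | 3, 156 | 68% | 79% | 0.216 |

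With only two time points, power at 160 is lower: 71%, 63% and 62%.

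**T1 to T2 change in SD units.** The SD of a change is SD × √(2(1 − r)), which equals one SD at r = 0.5. For a two-sided paired t test at alpha 0.05 and 80% power, the detectable change is
- n = 200: 0.199 SD, which agrees with f = 0.0995 (for two time points, d = 2f)
- n = 160: 0.223 SD
- n = 40, one sector: 0.454 SD

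**Categorical outcomes.** Exact McNemar, baseline proportion 0.45, correlation 0.5, odds ratio taken as marginal. At the stated sizes, power is 78.5% (OR 0.66, n = 200) and 82.6% (OR 0.39, n = 50), which is approximate agreement. At the Time 2 sizes it is 68% (n = 160) and 70% (n = 40).

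**The case against.** The strongest reply is that the two subsections after the disputed paragraph already give power for time, sector and sector by time, and that those figures reproduce. That stands: the study does have relevant power calculations. They do not support the claim at 40 per sector, however, because they are computed at 50. The loss is modest for change over time (0.20 to 0.22 SD) and larger for the sector contrasts.

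A second reply is that the label may simply have been carried over from another document, and that the article is open about the lack of randomization. Both may be so, and the text cannot settle the origin of the label. The paragraph still needs correcting. The fault lies in what it states, not in detail that an article may leave to a full protocol.

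Two stronger readings are tempting. A reader might infer that the 80% is power for a comparison of ERST with no ERST. The paragraph states no such contrast; it can only be guessed from the label. A reader might also treat the four sectors as clusters, two against two, and conclude that 80% is implausible. No such layout, effect or intraclass correlation is given, so that would test an invented trial. The documents show the figure to be uncheckable, not false.

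**Conclusion.** The point holds as a mismatch between the sample-size basis and the design. The 40 per sector and the power above 80% are attributed to a cluster randomized trial, while randomization was ruled out and no comparator is described. The absence of a control arm is read from Study design, Hypotheses, and Strengths and limitations together; no sentence calls the study single-arm.

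In size, at 160 participants all three stated continuous-outcome effects fall below 80% power. Time is only just short; the two sector contrasts fall short by about 9 and 12 percentage points. This rests on the article's alpha of 0.05 and correlation of 0.5, on reading its effects as Cohen's f, and on three time points with 40 per sector at each. The SD figures also assume a two-sided paired test and make no allowance for familywise error control or for sector as a random effect, for which the article gives no intraclass correlation.

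**What to change.** In Sample size requirements and power analyses, delete the cluster-randomized-trial calculation and its 80% figure. Replace them with text such as:

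*With 40 participants per sector (160 in total), alpha 0.05, a within-person correlation of 0.5 and three time points, the repeated-measures model has 80% power to detect effects of about f = 0.10 for time, 0.12 for sector by time and 0.22 for sector. For T1 to T2 within-person change, this sample has 80% power to detect about 0.22 SD overall and about 0.45 SD within one sector. These figures do not apply to a comparison of ERST with no ERST, because the study has no control arm.*

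The calculations at 50 per sector can stay, labelled as referring to the enrolled sample. The change is to wording only; it adds no participants and alters no hypothesis or test. Its downside is that the stated detectable effects become slightly less favourable.

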#### Longitudinal and cross-sectional continuous outcomes (e.g., PTSI symptoms)

Power associated with the sample size was calculated to determine the statistically significant effect size (the standardized difference in means). Repeated measures on ANOVA (with statistical software G*Power) used for the calculation, the calculations were based on statistical power of 80%, setting the sub-sample of 50 participants in each sector (total sample = 200), the nominal statistical significance level at α = 0.05, and the correlation within study participants (i.e., across repeated measurements) assumed to be 0.5. The PSP PTSI Study is well powered for small effect sizes; as such, the effect size should be > 0.10 for overall change from baseline to T2 and T3 (time as a main effect), > 0.11 when calculating differences between sectors (as an interaction effect with time), and > 0.19 when calculating overall differences between sectors (sector as a main effect).

